## Abstract

**Background:**

Primary treatment of carcinoma of the oro-/hypopharynx or larynx may consist of combined platinum-containing chemoradiotherapy. In order to improve clinical outcome (i.e. local control/overall survival), combined therapy is intensified by the addition of the EGFR inhibitor cetuximab (Erbitux^®^). Radiation therapy (RT) is carried out as intensity-modulated RT (IMRT) to avoid higher grade acute and late toxicity by sparing of surrounding normal tissues.

**Methods/Design:**

The REACH study is a prospective phase II study combining chemoradiotherapy with carboplatin/5-Fluorouracil (5-FU) and the monoclonal epidermal growth factor-receptor (EGFR) antibody cetuximab (Erbitux^®^) as intensity-modulated radiation therapy in patients with locally advanced squamous-cell carcinomas of oropharynx, hypopharynx or larynx.

Patients receive weekly chemotherapy infusions in the 1^st ^and 5^th ^week of RT. Additionally, cetuximab is administered weekly throughout the treatment course. IMRT is delivered as in a classical concomitant boost concept (bid from fraction 16) to a total dose of 69,9 Gy.

**Discussion:**

Primary endpoint of the trial is local-regional control (LRC). Disease-free survival, progression-free survival, overall survival, toxicity, proteomic and genomic analyses are secondary endpoints. The aim is to explore the efficacy as well as the safety and feasibility of this combined radioimmunchemotherapy in order to improve the outcome of patients with advanced head and neck cancer.

**Trial registration:**

ISRCTN87356938

## Background

Long-term outcome for patients with advanced squamous cell carcinoma of the head and neck (SCCHN) is still disappointing. For locally advanced or unresectable SCCHN without evidence of distant metastases, combined chemoradiotherapy is a proven curative treatment option. Due to the sometimes marked side effects in standard chemoradiation regimens using altered-fractionation 3 D conformal radiation techniques, intensification is rarely clinically possible. In view of further improvement of clinical outcome by intensification of the combined treatment approach, toxicity of the established treatment regimen needs to be reduced by employing modern radiotherapy techniques such as IMRT.

A meta-analysis from the MARCH Collaborative Group has shown an absolute survival benefit of 6.5% at 5 years for concurrent chemoradiotherapy [1]. A smaller yet still significant survival benefit was found for all chemoradiotherapy algorithms, whether it was neoadjuvant, adjuvant or concomitant with 4.5% at 5 years [1]. This effect was mainly caused by an increased local control and only to a lesser extent by reduction of distant metastases. The MARCH data showed no difference in response to chemoradiotherapy with respect to tumor site (oral cavity, oro-, hypopharynx, larynx). A published meta-analysis even found an overall survival benefit of 12 months when adding chemotherapy to normally fractionated radiotherapy or altered fractionated schedules [2]. However, no increased benefit was found when using hyperfractionated or accelerated fractionation [conventional fraction of 1.8 or 2.0 Gy per day] in this meta-analysis.

Altered fractionation schedules, especially hyperfractionation, lead to a significant improvement in overall survival if radiation therapy is performed as a single therapy modality. Accelerated radiation therapy alone, however, does not increase overall survival when given as split course or extremely accelerated treatments with decreased total dose. Bourhis et al. came to the same conclusion in their recent meta-analysis: the authors found that altered fractionation schedules showed only a small but again significant, absolute survival benefit when compared to conventional radiotherapy [3]. Also, survival benefit was significantly higher with hyperfractionated radiotherapy than with accelerated radiotherapy. In addition, altered fractionation regimen resulted in increased locoregional control in all patients though younger patients seemed to benefit most.

In view of the MARCH data regarding the type of chemotherapy, most positive trials combined radiotherapy with three cycles of concurrent cisplatin 100 mg/m^2 ^[1] which can be considered the standard regimen. Budach et al. revealed the highest prolongation of survival of 24 months in combining 5-FU and radiotherapy [2]. Cisplatin- and carboplatin-based chemotherapy and radiotherapy prolonged the survival to 16.8 and 6.7 months, respectively.

However, it is a clinical fact that a significant percentage of patients do not receive their full planned course of combination treatment due to excessive toxicity, hence the need arises to optimize these regimen. Various options exist: first of all, the use of more tolerable chemotherapy combinations, second the integration of molecular targeted drugs and third the use of modern concepts of radiotherapy.

Staar et al. combined carboplatin with 5-FU and hyperfractionated accelerated radiotherapy in a randomized phase III trial [4] and presented comparable results to studies based on cisplatin. The published acute and late toxicity was moderate in this trial.

Another option of a treatment combination is the addition of targeted therapy approaches e.g. antibodies or small molecules. Squamous cell carcinomas of the oro-, hypopharynx and larynx often show an overexpression of epidermal growth factor receptors (EGFR), which is described to be associated with a poor prognosis [5-7].

Cetuximab is a monoclonal antibody binding to the extracellular EGFR domain. Intracellular phosphorylation of the EGFR is inhibited and consequently the down stream signalling is deficient resulting in cell cycle arrest and increased expression of pro-apoptotic enzymes. Further effects of EGFR-inhibition that have been already published are a reduction of cell proliferation and angiogenesis, as well as an increase of apoptosis [8,9]. Cetuximab has been found to potentiate the effects of chemotherapy and radiotherapy in experimental systems [8-10].

In a clinical setting, Bonner et al., in a pivotal phase III trial, compared radiotherapy alone vs. radiotherapy combined with cetuximab. In this trial, a statistically significant increased overall survival and local control rate could be found for the combined treatment regimen [11,12]. Furthermore, beside skin reactions and a slight increase of infusion reaction no further severe side effects were reported. Apart from these medication specific side effects, no significantly increased toxicity caused by the combination of radiotherapy and cetuximab could be found. This study was the first to demonstrate in a clinical phase III setting that the combination of radiotherapy and a monoclonal antibody against the EGF-receptor resulted in a clear survival benefit. When comparing the results of the Bonner study with chemoradiotherapy studies, it can be assumed that comparable results could be achieved with this new combination. In a retrospective literature review of chemoradiation data, the Bonner regimen yielded comparable results, hence this treatment is an alternative for patients who might not complete standard therapy due to co-morbidities. Unfortunately though, there is no phase III trial evaluating RCT vs. RT + cetuximab yet.

A further possibility to improve the therapeutic ratio is the integration of modern techniques of radiotherapy in current treatment schedules. Techniques like intensity modulated radiotherapy (IMRT) can reduce the acute and late toxicity and allow, through better protection of the surrounding organs at risk, the application of higher doses without increased toxicity and higher conformity.

The REACH trial is a phase II trial evaluating the combination of modern radiotherapy techniques (IMRT) and standard chemotherapy with the EGFR-inhibitor cetuximab. The fractionation regimen applied for IMRT corresponds to the established accelerated-hyperfractionated regimen in conventional 3D-RT, hence the same doses per fraction and total dose are prescribed. Therefore, we would assume no increased risk concerning RT with this modern technique. It seems that IMRT in this specific set-up can even further reduce potential side effects. Hence, better local control rates could be achieved due to the advantages of IMRT in receiving a better dose distribution in the target volume.

## Methods/Design

### Trial organization/coordination

REACH is a single-treatment group, bi-centric trial designed by the study initiators of the Department of Radiation Oncology of the University of Heidelberg. In order to accelerate the data collection, the Helios Klinikum of Berlin Buch will also participate in this clinical trial. The trial is carried out by the Department of Radiation Oncology of the University of Heidelberg which is therefore responsible for overall trial management, trial registration (ClinicalTrials.gov Identifier: ISRCTN87356938), database management, quality assurance including monitoring and reporting. The trial is an investigator initiated trial (IIT). Trial medication cetuximab (Erbitux^®^) is supplied by Merck KGaA, Darmstadt, Germany.

### Investigators

Patients will be recruited by the Departments of Radiation Oncology at the University of Heidelberg and the Helios Klinikum of Berlin-Buch. Due to the multi-modal nature of the trial, all investigators are experienced oncologists in the fields of radiation oncology and medical oncology.

### Quality assurance

According to Good Clinical Practice (GCP) and other applicable guidelines and regulations the side monitoring will be carried out by an independent monitor contracted by the sponsor.

### Ethics, informed consent and safety

The final protocol was approved by the ethics committee of the Medical Faculty Heidelberg (AFmu-005/2009), the local ethics committee Berlin and the Paul-Ehrlich-Institute (PEI-registration number 789/01). This study complies with the Declaration of Helsinki in its recent German version, the Medical Association's professional code of conduct, principles of Good Clinical Practice (GCP) guidelines and the Federal Data Protection Act. The trial will also be carried out adhering to local legal and regulatory requirements.

Written informed consent is obtained from each patient in oral and written form before inclusion in the trial. Nature, scope and possible consequences of which will been explained by a physician. The investigator will not undertake any measures specifically required for the clinical trial until valid consent has been obtained.

### Study design

The REACH study is a prospective phase II study combining the monoclonal EGF-receptor antibody cetuximab (Erbitux^®^) with standard chemotherapy and loco-regional irradiation therapy as intensity-modulated radiation therapy (IMRT) in patients with locally advanced squamous-cell carcinomas of oropharynx, hypopharynx or larynx. Patients will be treated by the Department of Radiation Oncology and Radiation Therapy, University of Heidelberg, in co-operation with the Helios Klinikum Berlin-Buch.

The primary endpoint of the study is the local-regional control (LRC).

The secondary endpoints are disease-free survival (DFS), progression-free survival (PFS), overall survival (OS), acute and late radiation effects, adverse events, proteomics and genomics.

### Patient selection

A total of 60 subjects with locally advanced, previously untreated, primary non-metastatic, squamous cell carcinoma located in the oro-, hypopharynx or larynx will be included. Each subject will receive the trimodal treatment as described above [radiation therapy (IMRT), chemotherapy (carboplatin and 5-FU) and cetuximab].

Inclusion criteria:

• Signed written informed consent

• Age between 18 and 70 years

• Life expectancy > 6 months

• Histologically confirmed locally advanced (stage III or IV), non-metastatic squamous cell carcinoma of oro-, hypopharynx and larynx (T_2-4_, N_x_, M_0_)

• Oral cavity or oro-, or hypopharynx or larynx as the primary tumor site

• At least one uni-measurable lesion according to RECIST criteria

• Karnofsky Performance Status > 70%

• Adequate bone marrow, liver and renal function: wbc > 1.5 × 10^9^/l, THC > 100 × 10^9^/l, hb > 10.0 g/dl, Bili < 2.0 g/dl, SGOT, SGPT, AP, GGT < 3 × ULN, sCrea < 1.5 mg/dl

• Commitment to use of adequate contraception

Exclusion criteria:

• Previous chemotherapy, radiotherapy or surgery for carcinoma of the head and neck

• Nasopharyngeal carcinoma

• Prior exposure to EGFR pathway targeting therapy

• Patients with unstable cardiac disease despite treatment, congestive heart failure NYHA III/IV, significant neurological or psychiatric disorders including dementia or seizures, active disseminated intravascular coagulation, symptomatic peripheral neuropathy Common Toxicity Criteria (CTC) grade II or higher as well as ototoxicity CTC II or higher except if due to trauma or mechanical impairment due to tumor mass.

• Pregnant or breast-feeding women

• Known allergic/hypersensitivity reaction to any drugs scheduled for the study treatment

• Participation in other interventional trial within the last 30 days

• Surgery within the last 30 days

• Known drug abuse

• Other previous malignancy within 5 years, with exception of a history of a previous, adequately treated basal cell carcinoma of the skin or pre-invasive carcinoma of the cervix

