#### Chemotherapy

Carboplatin will be applied at a dose of 70 mg/m^2 ^body surface as a one-hour intravenous infusion on days 8-12 and 36-40 (corresponds to RT- week 1 and week 5 of RT, Figure 1).

5-FU will be applied at a dose of 600 mg/m^2 ^of body surface as an intravenous infusion over 24 hours on days 8-12 and 36-40.

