### Adverse events

Radiotherapy-related toxicities will be assessed using the NCI Common Toxicity Criteria (CTCAE v.3.0). Toxicity will be evaluated at baseline, weekly during radiation therapy (blood count, electrolytes, chemistry, clinical examination, patient visits) and at follow-up visits. Unacceptable toxicity is defined as unpredictable or irreversible grade 4 toxicity.

Expectable possible acute toxicities (up to 3 months after irradiation) comprise skin toxicity (desquamation, erythema, hyperpigmentation), nausea, vomiting, fatigue, weight loss, loss of appetite, pneumonitis, haematological toxicity with leucozytopenia, thrombozytopenia or anaemia. These symptoms could be treated medically and therefore usually resolve within 2-3 weeks. However, transient parenteral nutrition and hydration might be necessary in some cases. All acute toxicities should completely resolve within a few weeks post radiation therapy.

Decisions regarding cetuximab as well as chemotherapy dose adjustment will be made by using the guidelines below and are based on haematological parameters (ANC and platelets) monitored weekly during radiation before each dose of cetuximab and chemotherapy.

Expedited reporting will be carried out according to the local regulations.

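### Minor safety point: adequate marrow at entry is set on total white cells (> 1.5 × 10^9/l) with no neutrophil limit, although dosing is decided on neutrophils and platelets

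*Protocol article*

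**What the plan says.** The inclusion criteria (Protocol article, Patient selection) state the marrow requirement with parameters, numbers and units: "Adequate bone marrow, liver and renal function: wbc > 1.5 × 10^9^/l, THC > 100 × 10^9^/l", followed by a haemoglobin limit of 10.0 g/dl. THC is read here as the platelet count. No other inclusion or exclusion criterion mentions neutrophils.

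The Adverse events section works with a different white-cell measure. It says that dose decisions for cetuximab and chemotherapy "are based on haematological parameters (ANC and platelets) monitored weekly during radiation before each dose of cetuximab and chemotherapy". It refers to guidelines for those decisions, but the article does not print them, so no ANC cut-off appears anywhere in it. The same section lists "haematological toxicity with leucozytopenia, thrombozytopenia or anaemia" among the acute toxicities to expect.

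Under Drug supply, the Chemotherapy section gives carboplatin at 70 mg/m^2 "body surface as a one-hour intravenous infusion on days 8-12 and 36-40", with 5-FU at 600 mg/m^2 over 24 hours on the same days. The legend of Figure 1 starts radiotherapy on day 8 as well.

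**The concern.** Two counts govern haematological dosing in this trial: ANC and platelets. Platelets have an entry limit on the same parameter. ANC does not; the only white-cell screen is on the total count, at a level low enough that it cannot stand in for a neutrophil limit.

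A site that follows the criterion exactly can therefore enrol a patient whose neutrophils are already low and record the marrow as adequate. That patient is scheduled for two five-day courses of carboplatin and 5-FU together with cetuximab and radiotherapy, a combination for which the article itself expects a fall in white cells. What is at stake is the safety of a small number of patients. Nothing in the efficacy analysis depends on it.

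**Working it through.** The article derives no figure for this limit, so there is nothing of its own to reproduce. The check is direct arithmetic.

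**Inputs**
- Entry limit on total white cells (WBC): > 1.5 × 10^9/l (Patient selection).
- Entry limit on platelets: > 100 × 10^9/l (Patient selection).
- Entry limit on ANC: none stated.
- Parameters for dose decisions: ANC and platelets (Adverse events).
- Neutrophil share of white cells: not given. Assumed to be 40-80%.
- ANC reference value of 1.5 × 10^9/l: not given. Used only as a yardstick, because it is the number the criterion attaches to white cells.

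**Step 1. Entry limits on the dosing parameters.** One of two: platelets yes, ANC no.

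**Step 2. The bound that needs no assumption.** ANC = WBC × share, and the share cannot exceed 1, so ANC ≤ WBC. At a WBC just above 1.5, ANC is below about 1.5 whatever the share.

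**Step 3. Share needed for ANC to reach 1.5** (= 1.5 / WBC):

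| WBC (× 10^9/l) | Calculation | Share needed |
|---|---|---|
| 1.6 | 1.5 / 1.6 | 94% |
| 2.0 | 1.5 / 2.0 | 75% |
| 2.5 | 1.5 / 2.5 | 60% |
| 3.0 | 1.5 / 3.0 | 50% |

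**Step 4. ANC at the entry limit under the assumed share.** 1.5 × 0.40 = 0.60 and 1.5 × 0.80 = 1.20, so about 0.6-1.2 × 10^9/l.

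**Step 5. How far above the limit this reaches.** The WBC at which ANC equals 1.5 is 1.5 / 0.80 = 1.875 (about 1.9) for an 80% share and 1.5 / 0.40 = 3.75 for a 40% share. Patients with a WBC between 1.5 and somewhere in the range 1.9-3.75 × 10^9/l are eligible now and would not be under an ANC limit of the same number.

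**Step 6. When ANC is first sure to be seen.** Dose decisions use ANC monitored during radiation before each dose. Radiation and chemotherapy both start on day 8, so the first chemotherapy dose is covered. That check bears on dosing a patient who has already been admitted. The Work-up section places the eligibility check before inclusion, and no ANC limit is applied there.

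**The case against.** The strongest reply is that this is an omission in a condensed article. The full protocol is not shown, dose guidelines are mentioned but not printed, and haematological detail has evidently been cut. A white-cell limit is not wrong in itself, and nothing requires entry and dosing to use the same parameter. This stands in part: the unprinted guidelines cannot be held against the article. But the marrow criterion is not left open. It is printed with a parameter, a number and a unit, and the objection is to where that limit has been set.

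The second reply is that patients are already protected, because ANC is checked before every chemotherapy dose, including day 8. That is correct and lowers the risk considerably. It does not change who is admitted.

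The third is that the yardstick is borrowed. The article gives no ANC cut-off, and the 40-80% share is an assumption. Both are true. The bound ANC ≤ WBC depends on neither, but the article does not show that an ANC below 1.5 is unsafe.

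The fourth is that hardly anyone is affected. Earlier chemotherapy or radiotherapy for head and neck cancer excludes a patient, and the platelet, haemoglobin and Karnofsky limits screen further. This stands, and it is a main reason for the low severity.

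A reader might also infer more than the article supports:
- **That the two sections contradict each other.** They do not. One sets entry, the other dosing.
- **That the white-cell limit is a misprint for ANC.** This is possible but cannot be settled from the article.
- **That a low count would go unseen until treatment.** This is not shown. The article says "Toxicity will be evaluated at baseline, weekly during radiation therapy (blood count, electrolytes, chemistry, clinical examination, patient visits". The blood count is listed with the weekly visits, so a baseline ANC is neither promised nor ruled out.
- **That the day 1 cetuximab dose has no ANC check.** The wording is ambiguous, because day 1 precedes radiation. No gap is claimed.

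**Conclusion.** The point holds as a minor safety correction. As printed, the marrow criterion does not screen for one of the two counts on which dosing depends. It counts as adequate a patient whose ANC is below about 1.5 × 10^9/l, or 0.6-1.2 at the limit if neutrophils make up 40-80% of white cells. The first statement follows from neutrophils being part of the white cells; the range rests on the assumed share. The number of patients affected cannot be estimated, because the article gives no baseline counts, but it is likely to be small.

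It would be wrong to conclude that such patients go unprotected into chemotherapy, since the pre-dose ANC check comes first. It would also be wrong to read any consequence for the primary endpoint: the locoregional control estimate and its precision are untouched. Severity: low.

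**What to change.** Add an ANC limit to the same eligibility line, for example ANC > 1.5 × 10^9/l. The sponsor should confirm the value and align it with the trial's own dose guidelines, because the article does not supply one. If ANC was what the existing limit was meant to describe, replace the white-cell term by ANC instead. Either way, check it before inclusion on the blood count that the white-cell, platelet and haemoglobin limits already require.

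The cost is one line of text and a differential on that blood count. The downside is that at most a few patients become ineligible. The planned analysis does not change.

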### Work-up

Pathologically documented squamous cell oro-, hypopharynx or larynx carcinomas will be sent for surgical consultation. Patients receive a complete work-up including examination under anaesthesia, head and neck CT scans, chest x-ray, abdominal ultrasound and bone scan. In case operation is either surgically or medically impossible or the patient refuses to undergo the procedure, in- and exclusion criteria will be examined and eligibility will be analyzed. Should a patient meet the trial conditions, information about participation in the study including potential risks and benefits is given to the patient. As soon as written consent is obtained, patients can be included into the trial and the required documentation will be provided by the study centre (Studienzentrale Klinische Radiologie, Abt. Strahlentherapie und Radioonkologie, [name]).

After inclusion, each patient receives a RT-planning CT-scan in an individually-adjusted precision immobilisation devices.

If a patient refuses treatment within the REACH trial, standard combined chemoradiotherapy (Carboplatin/5-FU, without cetuximab) will be offered.

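### The bilirubin inclusion limit is printed in g/dl instead of mg/dl, so as written it excludes no patient

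*Protocol article*

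**What the plan says.** The Patient selection section of the protocol article has one inclusion criterion on organ function, introduced as "Adequate bone marrow, liver and renal function". The part that matters here reads "hb > 10.0 g/dl, Bili < 2.0 g/dl, SGOT, SGPT, AP, GGT < 3 × ULN, sCrea < 1.5 mg/dl". It contains five liver limits. Bilirubin is given as an absolute concentration in g/dl, directly after haemoglobin, which is also in g/dl. The other four are relative to the laboratory's upper limit of normal (ULN): "SGOT, SGPT, AP, GGT < 3 × ULN". The renal limit that closes the line is in mg/dl: "sCrea < 1.5 mg/dl".

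The Work-up section says how the criteria are used. For a patient who cannot have or declines surgery, "in- and exclusion criteria will be examined and eligibility will be analyzed". Those who qualify are then informed about the trial and can enter once they have consented in writing.

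No other section gives a bilirubin limit. Liver dysfunction comes up once more, in the Discussion, as one of several conditions that may predispose patients on cetuximab to more severe radiation dermatitis. No threshold is attached to it there.

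**The concern.** Grams per decilitre is the expected unit for haemoglobin but not for bilirubin. A ceiling of 2.0 g/dl is so high that it does not act as a limit, so the bilirubin part of the liver criterion has no effect as printed.

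What is at stake is who may enter. Every subject is to receive carboplatin, 5-FU and cetuximab with radiotherapy, and the Discussion itself treats liver function as relevant to cetuximab toxicity. Two centres recruit, and both need to apply the same limit. Taken literally, the text admits a patient with raised bilirubin provided SGOT, SGPT, AP and GGT all stay below 3 × ULN. That is the only kind of patient affected, because the enzyme limits screen independently of bilirubin.

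**Working it through.** The document derives no figure here, so there is nothing to reproduce. The check is a unit conversion followed by a test of plausibility.

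**Inputs from the Patient selection section**
- Bilirubin: below 2.0 g/dl
- Haemoglobin: above 10.0 g/dl
- SGOT, SGPT, AP, GGT: each below 3 × ULN
- Creatinine: below 1.5 mg/dl

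**Inputs assumed (the document gives no bilirubin reference range)**
- Bilirubin ULN: 1.0 to 1.3 mg/dl
- Bilirubin in severe jaundice: 20 to 50 mg/dl

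**Step 1: convert the printed limit.** 2.0 g/dl × 1000 mg/g = 2000 mg/dl.

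**Step 2: compare it with haemoglobin in the same unit.** 2.0 / 10.0 = 0.2. The printed ceiling would allow bilirubin up to one fifth, by mass, of the minimum haemoglobin concentration.

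**Step 3: compare it with severe jaundice.** 2000 / 50 = 40 and 2000 / 20 = 100. The printed limit is 40 to 100 times the assumed severe values, so nobody can fail it.

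**Step 4: put it on the scale of the enzyme limits.** Multiple of ULN = limit / ULN.

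| Assumed ULN (mg/dl) | As printed, 2000 mg/dl | Corrected, 2.0 mg/dl | Enzyme limit |
|---|---|---|---|
| 1.0 | 2000 × ULN | 2.00 × ULN | 3 × ULN |
| 1.2 | 1667 × ULN | 1.67 × ULN | 3 × ULN |
| 1.3 | 1538 × ULN | 1.54 × ULN | 3 × ULN |

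With the unit corrected, the limit is about 1.5 to 2.0 × ULN. That is a working threshold of the same order as the enzyme limits.

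**Step 5: ask whether the text extraction could have caused it.** The prefix in mg/dl survives for creatinine a few words later. Losing it for bilirubin alone, right after a correct g/dl for haemoglobin, fits a drafting slip better than damage to the text.

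**Step 6: look for a correction elsewhere.** The Work-up section refers back to the criteria without restating them, and the Discussion mentions liver dysfunction without a number. Neither overrides the printed limit.

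**The case against.** The strongest reply is that this is an obvious misprint with no competing reading. Under a heading about adequate liver function, a bilirubin ceiling of 2.0 makes sense only in mg/dl. The Investigators section describes all investigators as experienced oncologists, so no two of them would be expected to decide differently. This stands as a limit on the practical harm. It does not make the printed threshold right: the reader has to correct it silently, and a form or range check copied from the text would not.

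A second reply is that the document is a journal article. The section on ethics, informed consent and safety refers to a separate final protocol that was approved by the ethics committees and the Paul-Ehrlich-Institute. The slip may not exist there or on any screening form. This also stands: from the article alone one can say that the limit is wrong as printed, not that any patient was screened against it. But the point is not about detail left out of a condensed text. The article states a specific threshold and states it wrongly.

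Third, that bilirubin cannot reach 2000 mg/dl is general laboratory knowledge and not something the article says. That is so, and it is declared above as an assumption. With a margin of 40-fold or more, the conclusion does not depend on the exact range.

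Finally, nothing statistical follows from the error, and four enzyme limits remain in force. Both are correct and are the reason for the low rating.

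**Conclusion.** The concern holds, as a minor one. The printed bilirubin limit is too high by a factor of 1000, assuming mg/dl was meant, and this element of the inclusion criterion therefore excludes nobody. It is one of five liver limits; the other four still work.

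The conversion is exact. That no patient can fail the limit rests on an assumed clinical range for bilirubin and holds across any plausible one. That mg/dl was the intended unit is an inference from the creatinine unit in the same line and from the sensible value it gives; the approved protocol would have to confirm it.

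The patients affected are those with raised bilirubin and all four enzymes below 3 × ULN, and only if the text is applied literally. The local-regional control endpoint, the planned 60 patients and the Kaplan-Meier analysis are unchanged.

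**What to change.** Check the bilirubin limit in the approved full protocol and, if it confirms the intended unit, correct the criterion to below 2.0 mg/dl. Then make sure that any screening form and any range limit in the case report form use the same unit at both centres.

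The cost is one unit in one line and a check of the forms. Design, sample size and analysis stay as they are.
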